
### Overall data management

Management of trial data will be in accordance with a data management protocol, which has been developed and approved by the project’s advisory group. Data will be stored in accordance with the requirements of all ethics committee. Data will only be accessible to investigators listed on the ethics application and statisticians.

### Analysis and sample size

Analyses will be performed using an intention to treat approach, with ECEC services as the unit of analysis. Separate analyses will be performed at each follow-up time point (6 and 18 months). Intervention effects on the primary trial outcome (at each follow-up time point) will be assessed using a linear mixed effects regression model, which will include fixed effects for the treatment group (intervention vs control), the baseline value of the outcome and variables that are prognostic of the outcome (service size and geographical region). Multiple imputations will be performed for ECEC services not providing follow up data in accordance with the recommendation by White and colleagues [64] and presented as the primary analysis. Continuous secondary outcomes will be analysed using a linear mixed effects regression model similar to the primary outcome. Dichotomous secondary outcomes will be assessed using a logistic regression model. A sensitivity analysis will be undertaken, adjusting for service characteristics that appear imbalanced between groups at baseline (if this is present). Additionally we will plan to undertake a subgroup analysis examining potential intervention effect among services with the lowest baseline outdoor free play opportunities (specified as the lowest third quartile).

For the primary outcome (mean minutes of opportunities for outdoor free play), a sample of 100 ECEC services will enable us to detect an absolute difference of 25.34 min/day in the time children have the opportunity to spend in outdoor environments during free play assuming a standard deviation of 43 min with 80% power and an alpha of 0.05 based on previous research [65]. An additional 27 min of outdoor free play time will increase total outdoor free play time to > 1 h for many services, resulting in an additional 10 min of MVPA [13]. An increase of 10 min in MVPA in children aged 3 to 6 years has been found to have clinically significant beneficial effects on fat mass and peak bone mass [66, 67].

For the secondary outcome (the proportion of services implementing the recommended indoor-outdoor free play routines per day for an entire week), a sample of 100 ECEC services (50 per group) will enable us to detect an absolute difference of 27.50%, assuming that 31% of control services implement an indoor-outdoor program as recommended, with 80% power and an alpha of 0.05 based on previous research [65].

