### Participants and recruitment

#### Sampling frame

A list of all centre-based ECEC services (i.e. long day care and preschool services) located in the HNE Local Health District (LHD) of NSW, Australia (*n* = 440) will be accessed via NSW Centre for Population Health (CPH) records [33] and will serve as the study sampling frame. Within NSW, long day care services provide centre-based care for children from 6 weeks to under 6 years of age for 8 or more hours per day. Preschools typically enrol children between 3 and 6 years of age and provide care for 6 to 8 h per day. The HNELHD area encompasses major metropolitan centres and inner regional communities, with 14% of the population located in remote communities [34].

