### Randomisation and blinding

An independent statistician will set-up block randomisation using a computerised random number function to randomise services in a 1:1 ratio to either the intervention or usual-care control group. Block randomisation (2, 4 or 6) will be used to ensure group allocation is approximately equal. Allocation will be stratified by service type (long day care service or preschool) and service size (small < 80 child enrolments or large > = 80 or more child enrolments) given an association exists between these factors and the implementation of indoor-outdoor routines [20]. Randomisation will be undertaken following baseline data collection (T_0_), and Service Managers will be notified of their group allocation following baseline data collection.

The trial will be conducted as an open trial as it is not possible to deliver the intervention without revealing allocation to ECEC services and those delivering the intervention. Outcome assessors and those undertaking data analysis will remain blinded to service allocation. Outcome assessors will not have access to service allocation data and data analysis will be performed by a statistician not involved in the trial.

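### Service type is a randomisation stratifier but is left out of the primary model without explanation; it should be added as a fixed effect

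*Protocol article*

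**What the plan says.** Under Randomisation and blinding, the protocol article states: "Allocation will be stratified by service type (long day care service or preschool) and service size". The reason covers both factors at once: "given an association exists between these factors and the implementation of indoor-outdoor routines".

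Under Analysis and sample size, the primary model is a linear mixed effects regression with fixed effects for treatment group, baseline minutes and "variables that are prognostic of the outcome (service size and geographical region"). Service type is not on that list. Continuous secondary outcomes use a similar model and dichotomous ones a logistic regression. A separate sensitivity analysis is planned, "adjusting for service characteristics that appear imbalanced between groups at baseline (if this is present").

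Under Sampling frame, long day care is described as running 8 or more hours a day. Of preschools it says: "Preschools typically enrol children between 3 and 6 years of age and provide care for 6 to 8 h per day". The primary outcome is recorded during hours of operation.

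**The concern.** The design and the analysis disagree. Two factors are balanced by design for the same stated reason, yet only one of them enters the model, while an unstratified factor takes the other place. This is not a detail left for a statistical analysis plan, because the article names the covariates.

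Stratifying on a factor removes its contribution to the true sampling variance of the treatment difference. A model that omits the factor still counts that contribution as residual noise. If the factor predicts the outcome, the reported standard error then exceeds the true one, confidence intervals are too wide and the test rejects less often than its nominal level.

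The sensitivity analysis is unlikely to repair this. Stratified blocks keep type close to balanced, so a rule triggered by imbalance will seldom select it. Under randomisation, what that rule does select reflects chance rather than prognostic value.

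**Working it through.** **Inputs from the article (Randomisation and blinding; Analysis and sample size).** 100 services, 1:1, so 50 per arm; SD 43 min; alpha 0.05 (taken as two-sided; the article does not say); 80% power; blocks of 2, 4 or 6 within type-by-size strata. **Not in the article:** the share r² of residual variance that type explains after baseline minutes, size and region. It is varied from 0 to 0.20.

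**The plan's own figure.** The article says "a sample of 100 ECEC services will enable us to detect an absolute difference of 25.34 min/day". With 50 per arm, SE = 43 × √(2/50) = 8.60, and the difference detectable with 80% power is 8.60 × (1.960 + 0.842) = 24.09 min (24.33 with the t distribution). Power at 25.34 min is 83.8% (83.1% with t). The stated figure is therefore not reproduced exactly. That is a separate matter and does not bear on this point; 25.34 is used below only as the reference difference.

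**Effect of omitting type.** Here 43 is treated as the residual SD of the model without type.

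- Reported SE without type: 43 × √(2/50) = 8.60.
- SE with type, which is also the true SE under stratification: s = 8.60 × √(1 − r²).
- Inflation factor: f = 1/√(1 − r²).
- Type I error without type: 2 × [1 − Φ(1.96 f)].
- Power at 25.34: Φ(25.34/s − 1.96) with type; Φ(25.34/s − 1.96 f) without.

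| r² | SE with type | SE inflation | Type I, type omitted | Power, omitted | Power, included |
|---|---|---|---|---|---|
| 0 | 8.60 | 0% | 0.050 | 83.8% | 83.8% |
| 0.02 | 8.51 | 1.0% | 0.048 | 84.1% | 84.5% |
| 0.05 | 8.38 | 2.6% | 0.044 | 84.4% | 85.6% |
| 0.10 | 8.16 | 5.4% | 0.039 | 85.1% | 87.4% |
| 0.20 | 7.69 | 11.8% | 0.028 | 86.5% | 90.9% |

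Worked line for r² = 0.10: s = 8.60 × √0.90 = 8.16 and f = 1.054. With type, 25.34/8.16 − 1.96 = 1.15, giving 87.4%. Without, 3.11 − 2.07 = 1.04, giving 85.1%.

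**Simulation check** (6,000 trials per cell, n = 100, stratified permuted blocks of 2, 4 and 6, 40% of services in one type). With type omitted and no treatment effect, the mean reported SE was 8.59 against an empirical SE of 8.22 at r² = 0.10 (type I error 0.040), and 8.60 against 7.81 at r² = 0.20 (type I error 0.033). With type included and r² above 0, reported and empirical SEs agreed closely and type I error was 0.048 to 0.053. Bias was at most 0.05 min in every cell.

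**What r² means in minutes.** Assume a 60/40 split of types, within-type SD 43, a within-type baseline to follow-up correlation of 0.5, and the same type difference d at both times. The residual variance given baseline and type is 43² × 0.75 = 1386.75. Without type it is V − C²/V, where V = 1849 + 0.24d² and C = 924.5 + 0.24d².

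| d (min/day) | Residual variance, type omitted | Implied r² | SE inflation |
|---|---|---|---|
| 20 | 1409.6 | 0.016 | 0.8% |
| 40 | 1466.2 | 0.054 | 2.8% |
| 60 | 1534.0 | 0.096 | 5.2% |

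Under these assumptions even a 60-minute gap between types, more than twice the 25.34 min target, leaves r² just under 0.10. The lower and middle rows of the first table are therefore easier to reach than the last.

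**The case against.** The strongest reply is that the cost is small and in the safe direction. Baseline minutes are already in the model and absorb part of any stable difference between types. The estimate is unbiased, the test is conservative, and power at 25.34 min with type omitted stays at 83.8% or more throughout the range, above the planned 80%. All of that stands. It limits the size of the point but does not explain the mismatch between design and model.

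Four stronger readings are tempting, and the article does not support them.

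- A reader might infer that the protocol itself calls service type prognostic. It uses that word only for size and region. For type it states an association with implementing indoor-outdoor routines, so prognosis for outdoor minutes is a reasonable inference and no more.
- A reader might infer that the standard error is certainly too large. That depends on r², for which no figure is given; at r² = 0 nothing is lost.
- A reader might infer that the trial's covariate adjustment as a whole is data-driven. The primary covariates are named in advance; selection by imbalance is confined to one labelled sensitivity analysis.
- A reader might infer that day length caps the outcome by type. Preschool hours are described only as typical, and 6 to 8 h is 360 to 480 min, whereas the sample-size text expects totals of just over 1 h for many services. Nothing shows that the cap binds.

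**Conclusion.** The omission is plain on the face of the article: one of two stratifiers, chosen for the same reason as the other, is missing from a named covariate list, and no reason is given. Its consequence is conditional. If type explains residual variance beyond baseline minutes, size and region, the reported standard error is too large and some power is given away. For an assumed share of 0 to 0.20, inflation is 0% to about 12%, type I error falls from 0.050 to about 0.03, and the power forgone at 25.34 min is 0 to 4.4 percentage points (90.9 − 86.5). There is no bias and no added false-positive risk.

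These sizes rest on the assumed r², on the stated SD of 43 min and on a two-sided 5% test. They describe the linear model and should not be carried over to the logistic one. The imbalance-triggered covariate choice is a minor weakness that cannot alter the primary result. The change is worth making because it is nearly free.

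**What to change.** Add service type as a fixed effect to the primary model, beside treatment, baseline minutes and service size; region may stay as a further pre-specified covariate. Add service type to the secondary-outcome models as well.

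Do not require a baseline value in every secondary model. MOVERS is observed only at 6 months. The whole-week indoor-outdoor outcome has an essentially constant baseline: Eligibility demands at least one indoor-only free play session over five days, and any such session classifies a service as not implementing. Baseline adjustment belongs in the models for mean minutes and for the proportion of free play time with outdoor access.

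As a minor accompanying change, replace the sensitivity rule of "adjusting for service characteristics that appear imbalanced between groups at baseline" with a fixed list of prognostic characteristics already collected, such as hours of operation and area socioeconomic status.

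Cost: a short change of text in the protocol or analysis plan, one degree of freedom in the primary model, and no new data.

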#### Research trial governance

This study has employed a research co-production approach in the design of its aims, evaluation approaches and intervention design. An advisory group consisting of expert implementation and physical activity researchers, policy makers, health practitioners, and representatives from early childhood organisations will oversee all aspects of the trial. A project team consisting of research staff and health promotion practitioners will develop and operationalise implementation strategies and data collection components of the trial according to study protocol. The lead author together with the advisory group will oversee the project dissemination plan including all publications and reports to stakeholders. Authorship will conform to the International Committee of Medical Journal Editors (ICMJE) guidelines.

#### Trial discontinuation or modification

It is not anticipated that any events would occur that would warrant discontinuing the trial. Changes in government mandate related to COVID-19 restrictions may require modification to data collection or intervention delivery modality. Any unforeseen adverse events will be reported to HNE HREC (primary approval committee) and appropriate action taken to address the event. The trial registration record will be updated with any protocol modifications and any deviations from original protocol will be reported when publishing trial outcomes.

## Discussion

This trial is one of few RCTs to assess the effectiveness of strategies to increase the implementation of evidence-based physical activity practices at scale in ECEC services in Australia. This intervention applies an evidence-based theory mapping approach to intentionally select strategies and intervention modalities that are amenable to scaling up. If effective, this trial will provide a strategy that could be used to deliver support to increase evidence-based physical activity programs to increase the impact of health promotion programs in this setting.

## Data Availability

Study is a study protocol and no data is generated as part of the manuscript. Data sharing is not applicable to this article as no datasets were generated or analysed during the current study.

## Abbreviations

AIM: Acceptability Intervention Measure
BCTs: Behaviour Change Techniques
BCW: Behaviour Change Wheel
COM-B: Capacity, Opportunity & Motivation Models of Behaviour
CPH: Centre for Population Health
EBP: Evidenced Based Practice
ECEC: Early Childhood Education and Care
ERIC: Expert Recommendations for Implementing Change
FPR: Free Play record
GOGA: Get Outside Get Active
HNE: Hunter New England
HPO: Health Promotion Officer
HREC: Human Research Ethics Committee
ICER: Incremental Cost Effectiveness Ratio
ICMJE: International Committee of Medical Journal Editors
ISAT: Intervention Scalability Assessment Tool
LHD: Local health District
MVPA: Moderate-to-Vigorous Physical Activity
NSW: New South Wales
RCT: Randomised Control Trial
SES: Socioeconomic Status
TDF: Theoretical Domains Framework
UK: United Kingdom
US: United States
